### Motion capture system

The Human Performance Lab consists of 2000 sq. ft. of dedicated space designed for human movement analysis. The lab contains an 8-camera Motion Analysis MC system with Cortex 8 software (Motion Analysis Corp., Rohnert Park, CA) to collect MC data. This system represents the state-of-the-art technology in MC. The MC system cameras is Kestrel and they will be spread over an area of 5 x 3 x 2 meters.

### Data collection

Upon arrival for their data collection session, the participant’s identification number will be checked, and they will fill out the Brief Pain Inventory Short Form, which will serve to identify any confounding pain effects on the testing protocol [21]. To mitigate the effects of possible fluctuations in pain perception, the pain survey will be administered immediately prior to the start of data collection.

Radar Micro-doppler signatures and biomechanical MC data will be simultaneously collected as participants perform a series of functional activities. Combining MC and MDR data collection presents unforeseen challenges. MC techniques are widely known and have developed a level of sophistication that allows for flexibility when positioning equipment in the data collection volume and selection of a marker set. Conversely, MDR is direction-specific in regard to the position of the antennae which in turn dictates the primary plane of action for the experimental task. Since body segment velocities for all three tasks in this experiment are primarily in the sagittal plane it is necessary to align the experimental apparatus with the MDR signal axis (0 deg from center of antennae). Once aligned, the challenge is to select a marker set where the experimental apparatus doesn’t obscure markers. The solution is to place extra tracking markers on the pelvis, forearms (wrists), and head. These markers can then be used as reference points in Visual 3D to create virtual markers, which are then used along with the actual markers to create the skeletal model.

The marker set used to produce the Visual 3D skeletal model (virtual and actual) consists of 34 markers which are used to calculate all joint and segment angles, and their time derivatives. Bilateral lower-body markers consist of medial and lateral toes (2nd metatarsal and little toe), heel (calcaneus), medial and lateral ankle (malleolus), and medial and lateral knee (Tibial condyles). Trunk markers consist of right and left (R&L) anterior superior iliac spine, R&L posterior superior iliac spine, R&L shoulder (acromion), lower neck (C7), mid-trunk (T8), and sternal notch. Bilateral arm markers consist of the medial and lateral elbow (humeral medial and lateral epicondyles) and the wrist (radial and ulnar styloid processes). Head markers consist of the left and right zygomatic arches directly anterior to the inter-aural axis and top of the head.

Data from the ACLR and control groups will be collected by the MDR and MC systems simultaneously by a triggering system that matches the data collection on the time axis prior to the onset of movement. Participants will be asked to perform five trials of each of the following three tasks: Two-legged drop jumps (DJ2) from a low box (30cm), standing from a seated position, i.e., sit-to-stand (STS), and continuous gait on a treadmill. Participants will be asked to wear appropriate clothing and footwear for exercise training. Each task will be demonstrated by a research team member and participants will be given time to practice before data collection begins. Task order will be randomized, and all five trials of each task will be performed as a block. Participants will be given time to rest between practice and trial performances and in between trials during data collection to minimize fatigue effects. Any trial that deviates from the instructed methods will be evaluated and repeated before continuing. The three tasks will be completed in the frontal plane or 0 degrees with respect to the MDR.

The DJ2 task is usually performed without incident in clinically recovered patients during late or post-ACL reconstruction rehabilitation, while the STS and gait are typically applied earlier in the rehabilitation periods for patients who have not fully cleared rehabilitation. The three tasks selected are typical of ACLR rehabilitation, can be performed in any clinic, and cover a range of performance abilities.

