### Motion capture processing

MC data will be analyzed in two ways: 1) traditional MC data analysis will occur using variables extracted from averaged trial data, and 2) MC data will be subjected to the same machine learning algorithms outlined in the MDS processing section. The difference is that there are specific variables for MDS and MC. Extracted MC variables will include: internal rotation of the knee, pronation of the foot, the difference between inter-knee distance, forward displacement of the ACLR hip relative to the uninjured hip, sagittal and frontal hip and knee angular deficits at peak knee flexion angle, sagittal plane hip and knee displacement at peak knee extension angle, sagittal knee and hip displacements during weight acceptance, sagittal knee and hip displacement at midstance, and peak knee flexion and displacement. Data will be analyzed, and movement variables extracted from processed data using Visual 3D (C-Motion, Inc., Boyds, MD) and custom programs written in MatLab (The Mathworks, Inc., Natick, MA).

Traditional MC processing occurs by calculating inverse dynamics using Visual 3D and/or custom MatLab programs. Note that the selected tasks and variables represent measures that are expected to be identifiable using MDR, but not necessarily by MC. It is expected that MC will successfully measure the DJ2s, will be marginally successful at measuring STS, and will be unsuccessful at measuring gait speed on a level treadmill. The data will be processed using typical MC methods. MC data will be cleaned and preprocessed (including filling in missing data) using methods established for software programs Cortex 8 and Visual 3D. Data will be filtered using a 4th order, zero-lag low-pass Butterworth filter using MatLab filtfilt with a 10 Hz cutoff frequency.

The MC data will help us to effectively compare the accuracy of the MC system to that of MDR. Due to their heterogeneity, the two traditional sets of pre-processed data will not be statistically comparable. As such, we will use similar machine learning techniques to process the MC data, so that we are able to determine the accuracy and predictability of MC to correctly classify the ACLR group versus control. Accomplishing this will allow direct comparisons of discrimination, sensitivity and specificity for each of the techniques to successfully predict the control and ACLR groups.

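### As listed, both knee markers are tibial and no marker is on the thigh, so knee internal rotation and frontal knee angle cannot both be recovered from motion capture

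*Protocol article*

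**What the plan says.** The Data collection section of the protocol article describes the marker set behind the Visual 3D skeletal model, counting virtual and actual markers together. It "consists of 34 markers which are used to calculate all joint and segment angles, and their time derivatives".

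It itemises the set by body region:

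- Each leg: "medial and lateral toes (2nd metatarsal and little toe), heel (calcaneus), medial and lateral ankle (malleolus") and "medial and lateral knee (Tibial condyles").
- Pelvis: "right and left (R&L) anterior superior iliac spine, R&L posterior superior iliac spine".
- Rest of the trunk: "R&L shoulder (acromion), lower neck (C7), mid-trunk (T8), and sternal notch".
- Each arm: "medial and lateral elbow (humeral medial and lateral epicondyles) and the wrist (radial and ulnar styloid processes").
- Head: "left and right zygomatic arches directly anterior to the inter-aural axis and top of the head".

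Because the apparatus can hide markers, extra tracking markers are placed at the pelvis, wrists and head and serve as references for virtual markers. None is placed on the thigh.

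The Motion capture processing section then begins its variable list: "Extracted MC variables will include: internal rotation of the knee, pronation of the foot". The same list includes frontal as well as sagittal knee deficits at peak knee flexion. These variables belong to the MC arm of the MDR-versus-MC accuracy comparison.

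**The concern.** Knee rotation is the orientation of the shank relative to the thigh, so it needs independent information on both segments. With no femoral or thigh marker, the thigh can be built only from a hip centre derived from the pelvis and the two tibial markers. Those tibial markers also define the top of the shank. When the tibia turns under the femur, the constructed thigh axis turns partly with it. Some of the rotation then disappears and some reappears as a false frontal-plane angle.

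MC is the comparator in the superiority aim. If some of its knee inputs are distorted by marker placement, a better result for MDR could partly reflect that placement. The Discussion attributes MC's limit to measurement resolution, so such a handicap could be misread as a limit of the technology. Analysis cannot repair this afterwards, because thigh rotation about its own long axis would never have been recorded.

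**Working it through.** **Step 1. Is the list closed?** Inputs are the itemised markers in Data collection.

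- Legs: 2 × (2 toe + 1 heel + 2 ankle + 2 knee) = 14
- Trunk: 2 + 2 + 2 + 3 = 9
- Arms: 2 × (2 elbow + 2 wrist) = 8
- Head: 3
- Total: 14 + 9 + 8 + 3 = 34

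This reproduces the stated 34. No counted marker is left over for the thigh.

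**Step 2. Geometry.** Assumptions, not in the document: thigh 42 cm, shank 40 cm, tibial markers 2 cm below the joint centre, no skin movement. H is the hip centre, K the midpoint of the tibial markers, A the ankle midpoint, and m the lateral-minus-medial knee vector.

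- Thigh frame: z = (H − K)/|H − K|; x = m − (m·z)z, normalised; y = z × x.
- Shank frame: z = (K − A)/|K − A|; x from the two ankle markers in the same way.
- Knee angles: thigh-to-shank rotation, decomposed in the order flexion, frontal, rotation.

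| Flexion | True rotation 10, frontal 0: rotation read | frontal read | True frontal 10, rotation 0: frontal read | rotation read |
|---|---|---|---|---|
| 0 | 0.0 | 0.0 | 9.5 | 0.0 |
| 20 | 1.1 | 3.1 | 8.5 | 3.0 |
| 40 | 3.8 | 4.9 | 5.7 | 4.6 |
| 45 | 4.6 | 5.0 | 4.9 | 4.7 |
| 60 | 7.1 | 4.5 | 2.6 | 4.1 |
| 90 | 10.0 | 0.5 | 0.0 | 0.0 |

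All entries are in degrees. Placing the markers anywhere from 0 to 4 cm below the joint changes the rotation and frontal readings by less than 1 degree. At 2 cm, the sagittal angle is under-read by at most about 3 degrees (87.3 at a true 90).

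**Step 3. Why both cannot be recovered.** Take small angles and markers at joint level, with flexion f, true rotation r and true frontal angle a. The constructed thigh frame turns with the tibial pair, which leaves

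- rotation read ≈ sin f × (r sin f + a cos f)
- frontal read ≈ cos f × (r sin f + a cos f)

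Both readings are multiples of the same quantity, so only one combination of r and a is observed. Check at f = 60, r = 10, a = 0: rotation 10 × 0.866² = 7.5 and frontal 10 × 0.866 × 0.5 = 4.3. The full model with markers at joint level gives 7.5 and 4.4.

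**Step 4. With femoral markers.** When a medial-lateral femoral pair defines the thigh, the same model returns rotation 10.0 and frontal 0.0 at every flexion from 0 to 90 degrees. One pair per leg adds 2 × 2 = 4 markers, so 34 becomes 38.

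**The case against.** **It may be one wrong word.** The elbow pair in the same paragraph sits on the proximal bone (the humerus), and a knee pair described in parallel would be femoral. In that case the total stays 34 and the measurement problem disappears. This stands: the document does not settle whether the tibial landmark is real practice or a slip. The text as printed still needs correcting, because anyone following it literally would collect data that cannot be repaired.

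**The list may not be complete.** The 34 mix virtual and actual markers, and the hip centre needed to build a thigh is not among them. An article may also leave segment definitions and calibration to a fuller document. This weakens any claim that every point in the model is known. It does not rescue the two variables: a hip centre derived from the pelvis says nothing about thigh rotation, and the named reference sites for extra tracking are the pelvis, wrists and head. A virtual femoral point set from tibial markers would move with the tibia.

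**Rotation is not lost everywhere.** A reader might infer that knee rotation simply cannot be measured with this set. That is too strong. In the model, 7.1 of 10 degrees is read at 60 degrees of flexion and all of it at 90, and Task 2 (sit-to-stand) starts from a 90 degree thigh-shank angle. What is lost there is the frontal angle.

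**Most of the variables are little affected.** Many of the listed hip and knee variables are sagittal, and foot pronation, inter-knee distance and hip displacement are not shown to suffer. The article also says openly that its variables are not necessarily expected to be identifiable by MC. This limits the reach of the point but does not remove it for the two named knee variables.

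**Conclusion.** The point holds for the text as written. A marker set that sums to its own stated total has no femoral or thigh marker, yet the plan extracts two knee variables that this set cannot jointly recover.

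Near extension the rotation reading is close to zero by construction. At mid-flexion a true 10 degree rotation creates up to about 5 degrees of false frontal angle. At deeper flexion the frontal angle collapses, which matters because the plan reads that angle at peak knee flexion. These sizes rest on the assumed dimensions, the 10 degree input and the absence of soft-tissue artefact. With real skin movement, femoral markers would not perform as perfectly as the model shows.

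A reader might go further and infer that the MDR-versus-MC comparison is biased toward MDR by a material amount. The document does not support that. A handicap in that direction is plausible, but nothing in the article allows the loss of MC classification accuracy to be computed. The sample size and power figures are unaffected.

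**What to change.** 1. Confirm which bone carries the knee markers.
2. If the tibial wording is a slip, change it to the medial and lateral femoral epicondyles. The total stays 34 and the cost is one correction.
3. If it is real, add medial and lateral femoral epicondyle markers on both legs, restate the total as 38, and update the Visual 3D model so that thigh and shank have separate markers. This costs four reflective markers and a minute or two per session, with no new equipment or participants.
4. The article does not say whether anyone has been recorded with a tibial-only set. If so, do not drop the two variables for those participants alone, because the MC classifier would then have different inputs for different people. Use one common MC variable set for everyone in the primary MDR-versus-MC comparison. Report the knee rotation and frontal-angle results, and any MDR superiority claim that rests on them, with this limitation stated.

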### Task 1: Timed Two-Legged drop jumps (DJ2)

Participants will step off a 30 cm high box with their arms held across their chest, landing with both feet simultaneously such that the fall distance is equal to the box height. Participants have to immediately and without hesitation execute a vertical jump (no horizontal translation) upon landing from the box jump. The participant’s return to an upright stationary standing position following the jump marks the end of that trial. Five trials will be performed with 30–60 seconds of rest in between.

### Task 2: Timed Sit-to-Stand (STS)

Participants will be seated on a height-adjustable, armless, flat seat while maintaining a vertical trunk position with their arms held across their chest. Seat height will be adjusted to ensure a 90-degree angle between the thigh and shank with feet flat on the ground. Participants will stand up quickly to reach a vertical standing position. Maintaining the final vertical standing position marks the end of the trial. Five trials with 30–60 seconds of rest in between will be performed.

### Task 3: Gait speed

Preferred gait speed will be estimated by having participants perform three trials of timed walks on a 10-meter measured hallway at their preferred pace. Preferred gait velocity will be estimated as the average velocity (m/s) of the three trials. A single 2.5 minute-gait trial will be performed by participants on a level treadmill at their preferred gait velocity. Only the last 2 minutes of the gait trial will be used for analysis.

### Micro-Doppler signature processing

The process of extracting unique information from MDR begins with the construction of micro-Doppler signatures (MDS). There are various procedures for generating MDS that have been proclaimed as useful in helping discern between physical activities monitored by MDR. The most common approaches extract features from signatures constructed through time-frequency and cadence-frequency diagrams. After obtaining such signatures, activity classification often starts in the form of extracting features from the created signatures. One of the most prominent methods used when performing activity classification with MDR configurations is through the analysis of time-frequency representations of the received MDS. Time-frequency signatures implement the short-time Fourier transform (STFT) for analyzing MDS. After constructing signatures for each activity measured by the MDR, further processing is incorporated into the signatures for extracting unique information. A variety of methods have been employed in extracting features embedded in the signatures. There are two types of feature sets evaluated in this work. One type of feature is deemed “traditional,” being that they are handcrafted from the raw data. The other types of features are those extracted through machine learning techniques, such as dimensionality reduction. More specifically, we propose a dimensionality reduction technique that, as far as we have found, has yet to be implemented in the classification of human gait classification via MDR. We previously developed the micro-Doppler signature processing algorithm (mD-SPA) for processing the MDS to classify specific movement conditions [12]. We will apply the same algorithm to the three performance tasks discussed above in order to distinguish the ACLR group from the control group and determine the accuracy and predictability of the algorithm. This data will be used for comparison to the MC outcome data (outlined below). We will then calculate the sensitivity and specificity of MDR to the MC data to determine whether the participant is in the ACLR group or the control group.

### Motion capture processing

MC data will be analyzed in two ways: 1) traditional MC data analysis will occur using variables extracted from averaged trial data, and 2) MC data will be subjected to the same machine learning algorithms outlined in the MDS processing section. The difference is that there are specific variables for MDS and MC. Extracted MC variables will include: internal rotation of the knee, pronation of the foot, the difference between inter-knee distance, forward displacement of the ACLR hip relative to the uninjured hip, sagittal and frontal hip and knee angular deficits at peak knee flexion angle, sagittal plane hip and knee displacement at peak knee extension angle, sagittal knee and hip displacements during weight acceptance, sagittal knee and hip displacement at midstance, and peak knee flexion and displacement. Data will be analyzed, and movement variables extracted from processed data using Visual 3D (C-Motion, Inc., Boyds, MD) and custom programs written in MatLab (The Mathworks, Inc., Natick, MA).

Traditional MC processing occurs by calculating inverse dynamics using Visual 3D and/or custom MatLab programs. Note that the selected tasks and variables represent measures that are expected to be identifiable using MDR, but not necessarily by MC. It is expected that MC will successfully measure the DJ2s, will be marginally successful at measuring STS, and will be unsuccessful at measuring gait speed on a level treadmill. The data will be processed using typical MC methods. MC data will be cleaned and preprocessed (including filling in missing data) using methods established for software programs Cortex 8 and Visual 3D. Data will be filtered using a 4th order, zero-lag low-pass Butterworth filter using MatLab filtfilt with a 10 Hz cutoff frequency.

The MC data will help us to effectively compare the accuracy of the MC system to that of MDR. Due to their heterogeneity, the two traditional sets of pre-processed data will not be statistically comparable. As such, we will use similar machine learning techniques to process the MC data, so that we are able to determine the accuracy and predictability of MC to correctly classify the ACLR group versus control. Accomplishing this will allow direct comparisons of discrimination, sensitivity and specificity for each of the techniques to successfully predict the control and ACLR groups.

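### Peak and at-peak motion capture variables should be extracted trial by trial and then averaged; extracting them from averaged trials understates peaks by an amount that depends on timing spread

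*Protocol article*

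**What the plan says.** The Motion capture processing section of the protocol article describes two analyses of the motion capture (MC) data. In the first, "traditional MC data analysis will occur using variables extracted from averaged trial data". In the second, MC data go through the machine learning used for the radar signatures. The averaging phrase belongs to the first analysis only.

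The section lists nine variables. Three involve a peak:
- "peak knee flexion and displacement"
- "sagittal and frontal hip and knee angular deficits at peak knee flexion angle"
- "sagittal plane hip and knee displacement at peak knee extension angle"

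The other six are knee internal rotation, foot pronation, inter-knee distance, forward hip displacement, displacement during weight acceptance and displacement at midstance.

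On repetitions, Data collection says: "Participants will be asked to perform five trials of each of the following three tasks". The Task 3 section differs for gait: "A single 2.5 minute-gait trial will be performed by participants on a level treadmill". Averaging over five trials therefore applies to the drop jump (DJ2) and sit-to-stand (STS). For gait it could only be over strides.

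On timing, MC and micro-Doppler radar (MDR) data are collected simultaneously "by a triggering system that matches the data collection on the time axis prior to the onset of movement". The article does not say how repeated trials are lined up with each other before averaging.

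**The concern.** The order of the two steps matters for a peak. If five curves are averaged first, a peak that falls slightly earlier in one trial and later in another is smeared, and the maximum of the mean curve is lower than the peak the participant typically reaches. The extracted number is then a mixture of how far the knee flexed and how consistently it was timed. A hip or knee angle read at the peak of the mean curve is taken at an instant that may not be the peak of any trial, and its error has no fixed direction.

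At stake is the interpretation of a group difference in these variables. Suppose one group has the same true peaks but less consistent timing. It would show lower extracted peaks, and this could be described as reduced flexion. A real difference could equally be masked or enlarged.

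**Working it through.** **The plan's own figures.** The article states no figure on this point. Its power figures concern classification accuracy and do not bear on it.

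**Direction (no assumption needed).** Let x_i(t) be trial i's curve, i = 1 to 5. At every t, the mean of the x_i(t) is at most the mean of the individual maxima, because each x_i(t) is at most max x_i. Hence

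max over t of mean x_i(t) ≤ mean of max x_i(t),

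with equality only if all five trials peak at a common instant. Extracting per trial and then averaging gives the right-hand side directly.

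**Size (all inputs assumed; none is in the article).** Knee-flexion excursion A = 70 degrees, Gaussian shape, width at half height W = 0.30 s, five trials with identical true peaks, and peak times varying with SD s.

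- Curve SD: c = W / 2.355 = 0.30 / 2.355 = 0.1274 s.
- Five trials share their own mean timing, so the spread around it has variance (4/5)s². The approximate loss is A × [1 − c / √(c² + 0.8s²)].
- s = 0.02 s: √(0.01623 + 0.00032) = 0.1286; 70 × (1 − 0.1274/0.1286) ≈ 0.7 degrees.
- s = 0.05 s: √(0.01623 + 0.00200) = 0.1350; 70 × (1 − 0.1274/0.1350) ≈ 3.9 degrees.
- s = 0.10 s: √(0.01623 + 0.00800) = 0.1557; 70 × (1 − 0.1274/0.1557) ≈ 12.7 degrees.

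Simulating the five curves and comparing the maximum of the mean with the mean of the maxima agrees, except that the approximation runs slightly high at the largest spread:

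| Timing SD | Simulated loss (W = 0.30 s) |
|---|---|
| 20 ms | 0.7 degrees |
| 30 ms | 1.5 degrees |
| 50 ms | about 4 degrees |
| 75 ms | about 8 degrees |
| 100 ms | about 12 degrees |

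At 50 ms the loss is 5.4 degrees for W = 0.25 s and 2.3 degrees for W = 0.40 s.

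A second set of assumed curves (20 to 90 degrees; curve SD 0.10, 0.15 and 0.20 s) gives losses of 1.1, 0.5 and 0.3 degrees at 20 ms; 6.0, 3.0 and 1.7 degrees at 50 ms; and 16.7, 10.0 and 6.0 degrees at 100 ms. Per-trial extraction returns 90.0 degrees in every case.

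**A group difference from timing alone (conditional).** With identical true peaks and W = 0.30 s, the artefact is the difference between two losses. Timing SDs of 30 and 50 ms give about 4.0 − 1.5 = 2.5 degrees. SDs of 50 and 75 ms give about 8 − 4 = 4 degrees. If the groups are equally consistent, the expected artefact is zero.

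**Effect of alignment.** Here s is the timing spread left after whatever alignment is used. Lining trials up at an event such as initial contact reduces s, but the time from that event to peak flexion still varies. Only alignment at the peak itself brings the loss to zero.

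**The case against.** The strongest reply is that a condensed article is being read too literally. The phrase does not expressly say that time-series curves are averaged, and it may be shorthand for participant-level means of extracted values. The section also refers to typical MC methods, and variables defined at weight acceptance or midstance imply that movement events are identified. Alignment details belong in the full protocol, so their absence is not a fault. All of that stands, and it limits the size of the effect. It does not change the order of steps as written. If per-trial extraction is intended, the sentence says the reverse and needs the same correction.

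Several stronger readings are tempting and are not supported:

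- *That most listed variables are affected.* Three of nine are peak or at-peak, and the direction of the error is fixed only for the peak itself.
- *That misalignment is built into the design.* The trigger synchronises MC with MDR; it is not described as the time base for averaging trials. A DJ2 trial does end when the participant's "return to an upright stationary standing position following the jump marks the end of that trial", so rescaling whole trials to a common length would leave landing times scattered, but the article does not say that it rescales this way.
- *That a false ACLR deficit is likely to be declared significant.* High rejection rates can be produced with an unadjusted t-test on peak flexion, but the data analysis section specifies no such test. Its mixed models are for task times and gait speed. Nor does the article show that ACLR participants are less consistent in timing than controls.
- *That the MDR-versus-MC comparison is biased against MC.* That comparison rests on the machine learning analysis, which is not stated to use averaged trials. The section leaves unclear whether the extracted variables feed the MC classifier.

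**Conclusion.** The concern holds for the traditional MC analysis of DJ2 and STS, and for three of its nine listed variables. That an averaged curve cannot overstate the mean peak, and understates it whenever trials peak at different times, is a mathematical fact. The size is not known from the article. Under the assumed 70-degree, 0.30 s curves with five trials, it runs from under 1 degree at 20 ms of residual timing spread to about 12 degrees at 100 ms, so it may be negligible with good event alignment and material without it. A spurious group difference arises only if timing consistency differs between ACLR and control participants, which the documents neither show nor exclude. Any effect on the MDR-versus-MC comparison depends on the same extracted variables entering the MC classifier. For treadmill gait, a single trial, the issue could arise only through averaging strides. The written order is worth correcting because the alternative is less biased and almost free.

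**What to change.** In Motion capture processing, replace the averaging phrase with: *MC variables will be extracted from each trial (each stride for gait) at that trial's own event, and the extracted values will then be averaged per participant.* If extracted variables enter the MC classifier, state that and use the same per-trial values there. Averaged curves can be kept for display.

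The cost is one sentence and the swapping of two steps in the Visual 3D and MatLab processing, with no new data or participants. The small downside is that single-trial peaks are slightly noisier. The planned 10 Hz low-pass filter and the averaging of five extracted values limit this.
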